### Statistical methods

A data management and statistical analysis plan has been developed during the preparations leading up to the trial. This details the procedures for data quality assurance and quality control (including standard operating procedures), data entry, management and cleaning, and data analysis (including *a priori* comparisons, interim analyses, and Data Safety and Monitoring Board (DSMB) instructions).

Data will be entered at the time of interview via handheld devices (cell phones) and automatically stored in a secure firewall-protected database. Data analysis will take place using the latest version of STATA (College Station, Texas, USA). All analyses will be blinded until the analysis is finalized and approved by all investigators. Data cleaning based on frequency distributions and logic checks will follow standard procedures with reference to source documents as required. Exploratory analyses will include frequency distributions and measures of central tendency and dispersion, as appropriate, with 95% confidence intervals. Throughout these analyses, stratifications will be by participant age, and depression severity at enrollment. Throughout, bivariate comparisons will employ χ^2^, Fisher’s exact, student’s T- or rank-sum tests, as appropriate; all statistical tests will be two-sided at α = 0.05. The primary analysis will be by intention-to-treat, and secondary analyses will be on a per protocol population, defined as women who complete all sessions in either arm of the trial. The primary outcome measure will be analyzed using linear regression adjusting for baseline symptom severity measured using the HDRS-17. The validity of regression assumptions will be checked using residual plots. Logistic regression will be used to model some secondary outcomes, which are measured on a binary scale.

In relation to the economic analysis i) costs associated with delivering the task sharing intervention, as well as the consequential impact on service use, will be analyzed using multiple regression analysis; bootstrap methods will be used if the residuals of the regression model are non-normally distributed. ii) Further regression models will include the main clinical measures so that the relationship between costs and outcomes can be assessed.

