**Methods/Design:**

The study is an individual-level two-arm RCT. A total of 420 depressed pregnant women will be recruited from two ante-natal clinics in a low-income township area of Cape Town, using the Edinburgh Postnatal Depression Scale to screen for depression; 210 women will be randomly allocated to each of the intervention and control arms. The intervention group will be given six sessions of basic counseling over a period of 3 to 4 months, provided by trained community health workers (CHW)s. The control group will receive three monthly phone calls from a CHW trained to conduct phone calls but not basic counseling. The primary outcome measure is the 17-Item Hamilton Depression Rating Scale (HDRS-17). The outcome measures will be applied at the baseline assessment, and at three follow-up points: 1 month before delivery, and 3 and 12 months after delivery. The primary analysis will be by intention-to-treat and secondary analyses will be on a per protocol population. The primary outcome measure will be analyzed using linear regression adjusting for baseline symptom severity measured using the HDRS-17.

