##### Participants: counseling intervention

Participants randomized to the intervention arm will receive the structured manual-based psychological treatment by the trained CHWs, who are known and accepted within the local community. They will receive six counseling sessions (of approximately 1 hour in duration each), which include aspects of psycho-education, PST, behavioral activation, cognitive reframing (healthy thinking), and relaxation training. This has been informed by a review of the available literature, and formative qualitative research conducted in the 12 months preceding the trial, which indicated the need for problem solving skills, extending the range of social support and usual activities through behavioral activation, and cognitive reframing to address patterns of persistent negative cognitions. The intervention was also informed by similar manuals developed in the field and consultation with co-investigators.

The counseling sessions will be conducted approximately every 2 weeks at the clinic or at the participant’s home (by prior arrangement). Counseling sessions will be scheduled to align as closely as possible with routine antenatal check-ups at the clinic. All counseling sessions will be initiated antenatally, but if the mother is enrolled in the study late in her pregnancy or delivers her baby early, the sessions may continue into the postnatal period, until all six sessions are completed. As part of the intervention, CHWs have been trained to follow-up women with maternal depression who miss sessions and encourage them to participate in the counselling sessions. This follow-up will include phone calls to the woman if a session is missed. During the phone call counselors will explore reasons for missing the session and help the woman to overcome barriers that may be preventing her from attending. A drop-out will be defined as a woman who misses three consecutive counselling sessions.

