##### Participants: control intervention

Participants randomized to the control group will receive enhanced usual care. Usual care involves attendance at antenatal and postnatal clinics on a voluntary basis, where the focus is on fetal and infant physical development and immunization. Enhanced usual care will comprise, in addition to usual care, regular monthly telephone calls over 3 months, delivered by two CHWs trained in conducting structured phone calls but not trained in counseling techniques. The telephone calls by the CHWs will engage participants in a brief conversation about i) how the woman is feeling (general health question); ii) whether there are any major changes in the woman’s life and, if so, what these are (including starting any medication); iii) whether she has someone to assist her if she needs help; iv) whether she or her baby have been visited by any community workers from other organizations and description of these visits; and v) whether there is suicidal ideation. If there are signs of major problems (e.g., abuse or other social difficulties), participants will be provided with contact details of relevant health services and NGOs. If there are signs of suicidal ideation, they will be referred to the psychiatric nurses at the clinic. Similarly to the intervention arm, unless their health or behavior makes it impossible for them to continue to receive the telephone calls or participate in follow-up assessments, suicidal participants will be retained in the study.

In determining the optimal number and frequency of phone calls to the women in the control arm, a balance needs to be retained between the need to monitor any adverse changes in the women’s mood, and not being too intrusive or providing too intensive an intervention that would not represent usual care. Following formative research and discussion with the research team, it was decided that monthly telephone calls given over 3 months (in keeping with the timing of the counseling intervention) are sufficiently frequent to monitor any major changes in mood, offer referrals, and provide information about services and thereby constitute enhanced usual care.

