### Sample size and power calculation

The sample size of 420 women (210 in each arm) is based on the following assumptions: two-sided testing at alpha = 0.05, beta = 0.1 (i.e., 90% power), and a 30 to 50% reduction in depressive symptoms at 3 months postnatally as measured by the HDRS-17 in the control arm based on enhanced usual care. Absolute effect sizes of interest range from 20 to 40%. Based on previous cohort studies and trials in mental health care in this community, we feel that 10% attrition over the study period is realistic. In addition, we conservatively estimate contamination between the trial arms of the order of 5% (that is, 5% of women in the control arm will experience the treatment effect of the intervention through exposure to women in the intervention arm). Based on these assumptions, we estimate that 420 women in the trial will be required to detect an intervention effect of 20% or greater between the two arms.

The sample of 420 women makes provision for subjects that might move away or refuse to take part in the study at a later stage. If subjects in the study drop out or are unable to continue participating in the trial they will not be replaced. Drop out from care is defined as three consecutive missed appointments, for either the counselling sessions or telephone calls. We will endeavor to continue to collect data from people who move out of the area provided they give informed consent to continued participation, and can be contacted. After a participant has missed five consecutive follow-up assessment appointments for a specific assessment point, they will be deemed to have dropped out of the study.

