### Ethical considerations

Ethical approval for research with human subjects was obtained from the University of Cape Town Human Research Ethics Committee (Ref no 226/2011) and the National Institute of Mental Health (NIMH) DSMB prior to the start of recruitment. Each participant is providing informed consent prior to participation in the trial. On the whole, the trial will pose minimal risks to the participants. In order to minimize risk, careful training and supervision of the counselors and field workers will occur. A monitoring system is in place for adverse and serious adverse events, with a protocol for the management of these events and reporting at appropriate times to the DSMB. Participants will be asked about suicidal ideation at all contacts (including intervention and control sessions and all baseline and follow-up assessments), and if participants report suicidal ideation, a protocol is in place for referral to the psychiatric nurses at the clinic. Unless their health or behavior makes it impossible for them to continue to receive counseling sessions or participate in follow-up assessments, suicidal participants will be retained in the study. Uptake of psychiatric services by these participants will be monitored for both groups.

Quality assessment of the study will occur at a number of levels:

The mental health counselor will oversee the training, supervision, and support of the CHW counselors and CHWs telephoning the control group participants. They will hold regular individual and group supervision sessions to review sessions completed and issues arising.Further refresher training will be provided if this is deemed necessary at any given point in time.The research officer will train, supervise, and support the assessment team in the baseline and follow-up assessments.All data from the baseline and follow-up assessments and reports from sessions (e.g., dates, length of session, manual topic covered) will be captured using mobile technology. The database will be reviewed on a continuous basis by unblinded members of the team to check on quality.The trial statisticians will be asked to review the data at key points during the life of the trial.

Reports will be submitted to the NIMH DSMB twice per year for external control of quality. All serious adverse events will be reported to the NIMH DSMB within 48 hours of being reported to the trial team.

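### The per-protocol set requires six counselling sessions in one arm but three phone calls in the other, so it is likely to select women differently by arm; the direction of any bias is not settled

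*Protocol article*

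**What the plan says.** All references are to the protocol article.

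- **Analysis sets** (Statistical methods): the main comparison follows intention-to-treat. The per-protocol set is fixed as follows: "secondary analyses will be on a per protocol population, defined as women who complete all sessions in either arm of the trial". For HDRS-17, the main outcome, the stated model is "linear regression adjusting for baseline symptom severity measured using the HDRS-17".
- **Counselling arm** (Participants: counseling intervention): "They will receive six counseling sessions (of approximately 1 hour in duration each".
- **Control arm** (Participants: control intervention): "regular monthly telephone calls over 3 months, delivered by two CHWs". The abstract gives the number of calls as three.
- **Calls count as sessions** (Ethical considerations): suicidal ideation is asked about "at all contacts (including intervention and control sessions and all baseline and follow-up assessments", so the article itself uses the word for both arms.

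No minimum number of sessions short of all of them is offered as an alternative definition, and the article does not say how completion relates to prognosis.

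**The concern.** A single label covers two different tests. A woman in the counselling arm must complete six hour-long contacts to stay in the set; a control must complete three calls. Completion happens after randomisation. If it is related to prognosis, the two groups of completers are filtered to different degrees and the comparison is no longer protected by randomisation. A woman who attended five of six sessions is excluded although she received most of the treatment.

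This is the only named secondary population and the only stated analysis that bears on the effect of actually receiving counselling. The article's Discussion says the findings are meant to inform policy makers, who may well ask that question. The definition is fixed in the article, so it is not a detail left to an analysis plan that is not shown.

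**Working it through.** The article gives no figure for the size or bias of this set, so there is nothing to reproduce. The two illustrations below rest on assumed attendance.

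**1. Share retained.** From the article: 210 women per arm, six sessions, three calls. Assumed: independent contacts with the same completion probability q in both arms. The share completing everything is q⁶ against q³.

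| q | Counselling, q⁶ | Control, q³ | Women of 210 |
|---|---|---|---|
| 0.80 | 26% | 51% | 55 v 108 |
| 0.85 | 38% | 61% | 79 v 129 |
| 0.90 | 53% | 73% | 112 v 153 |
| 0.95 | 74% | 86% | 154 v 180 |
| 0.98 | 89% | 94% | 186 v 198 |

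At equal q the counselling arm is always the more heavily filtered.

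**2. Completer difference when there is no treatment effect.** Assumed: latent prognosis U is standard normal, with higher values worse. The outcome is Y = 0.5U + e with SD 1. Attendance per contact is p = Φ(a − bU), with a set so that mean attendance is 0.85. A woman is kept with probability p⁶ (counselling) or p³ (control). With 2,000,000 simulated women, the difference (counselling minus control; negative favours counselling) is:

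| b | Kept, counselling v control | Difference |
|---|---|---|
| 0.2 | 39% v 62% | −0.07 SD |
| 0.3 | 41% v 63% | −0.09 SD |
| 0.5 | 46% v 64% | −0.11 SD |

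**3. Adjusting for baseline.** Add a baseline score correlated r with U and include it in the regression, for b from 0.2 to 0.5:

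- r = 0.5: the bias is about 0.055 to 0.085 SD.
- r = 0.7: the bias is about 0.04 to 0.06 SD.
- Over both, allowing for simulation error, about 0.035 to 0.085 SD remains.
- r = 0.9: about 0.02 SD remains.

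**4. Varying the assumptions** (unadjusted unless stated):

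- Attendance unrelated to prognosis (b = 0): about 0.
- Worse-off women attend more (b = −0.3): +0.09 SD, against counselling.
- Counselling attendance 92% and call completion 85% (b = 0.3): 63% kept in each arm, bias about −0.015 SD. At 90% v 80%: about −0.01 SD.
- Attendance 95% in both arms, baseline adjusted with r = 0.5: 74–76% v 86–87% kept, bias about −0.02 to −0.04 SD.

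**5. A yardstick.** The article states its target as a 20% effect, not in SD units. From its power inputs (210 per arm, 10% attrition, 90% power, two-sided 5%, 5% contamination), n = 210 × 0.9 = 189 per arm. The detectable standardised difference is (1.960 + 1.282) × √(2/189) = 0.333, and allowing for dilution 0.333 / 0.95 = 0.351 SD. Against this, 0.07–0.11 SD is about a fifth to a third, and 0.035–0.085 SD is 10–24%.

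**The case against.** The strongest reply is that six against three does not fix the sign. A reader might infer that the set is biased towards the intervention. The documents do not support that as a fact: it needs completers to have better prognosis and the filter to be stronger in the counselling arm, and the article states neither. More symptomatic women might engage more with counselling, which reverses the sign. The article also describes retention effort in the counselling arm: calls after a missed session, home sessions by arrangement, alignment with antenatal visits, and continuation after delivery until the course is finished. It describes no matching effort for missed control calls. Higher attendance per contact in the counselling arm could offset the longer schedule. All of this stands.

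It is also fair that an unadjusted simulation overstates the problem, because the stated model for the primary outcome includes baseline HDRS-17. Adjustment shrinks the illustrated bias but does not remove it unless baseline captures nearly all the relevant prognosis.

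A reader might also point to the drop-out rule, "Drop out from care is defined as three consecutive missed appointments, for either the counselling sessions or telephone calls", which is half the sessions in one arm and all the calls in the other. That is true, but nothing in the article uses the rule to form this or any other analysis set, so it adds nothing here.

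Finally, the set is secondary and the article claims no causal meaning for it. That limits the consequence. It does not repair a comparison whose bias cannot be signed from the design.

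**Conclusion.** The point holds in a limited form. The plan writes in a post-randomisation filter that is unequal between the arms. It is likely to select women differently, and the completer comparison may be biased, plausibly but not certainly towards the intervention.

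Under one set of assumptions the spurious benefit is 0.07–0.11 SD unadjusted and about 0.035–0.085 SD after baseline adjustment. Other assumptions, equally compatible with the article, give a bias near zero or of opposite sign. All these sizes depend on assumed attendance and an assumed link with prognosis; only the numbers of contacts and the sample size come from the article. A reader should not infer that the trial's main conclusion is at risk: that rests on the intention-to-treat analysis. The change is worth making, but it is not critical.

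**What to change.** For the secondary question of the effect of receiving counselling, replace the completer comparison with a complier-average (instrumental-variable) analysis of HDRS-17 at 3 months postnatally:

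- all randomised women with outcome data, as allocated;
- allocation as the instrument;
- receipt defined as reaching a number of counselling sessions fixed before unblinding, with controls coded as not receiving;
- baseline HDRS-17 as covariate.

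State the assumptions. One is exclusion: allocation acts on the outcome only through receipt as defined, so attendance below the threshold is taken to have no effect. The other concerns contamination: the sample-size section allows for 5% of controls experiencing the treatment effect, so coding every control as unexposed needs a sensitivity analysis. Without covariates the estimate is the intention-to-treat difference divided by the difference in receipt between arms, so a 5% exposure among controls lowers that divisor by 0.05.

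If the all-sessions comparison is kept, label it descriptive and report the number retained in each arm.

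The cost is a change of wording and one two-stage model in Stata. Ethical considerations says session reports are already captured electronically. The downside is a wider interval and reliance on the instrumental-variable assumptions.

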### Ethical considerations

Ethical approval for research with human subjects was obtained from the University of Cape Town Human Research Ethics Committee (Ref no 226/2011) and the National Institute of Mental Health (NIMH) DSMB prior to the start of recruitment. Each participant is providing informed consent prior to participation in the trial. On the whole, the trial will pose minimal risks to the participants. In order to minimize risk, careful training and supervision of the counselors and field workers will occur. A monitoring system is in place for adverse and serious adverse events, with a protocol for the management of these events and reporting at appropriate times to the DSMB. Participants will be asked about suicidal ideation at all contacts (including intervention and control sessions and all baseline and follow-up assessments), and if participants report suicidal ideation, a protocol is in place for referral to the psychiatric nurses at the clinic. Unless their health or behavior makes it impossible for them to continue to receive counseling sessions or participate in follow-up assessments, suicidal participants will be retained in the study. Uptake of psychiatric services by these participants will be monitored for both groups.

Quality assessment of the study will occur at a number of levels:

The mental health counselor will oversee the training, supervision, and support of the CHW counselors and CHWs telephoning the control group participants. They will hold regular individual and group supervision sessions to review sessions completed and issues arising.Further refresher training will be provided if this is deemed necessary at any given point in time.The research officer will train, supervise, and support the assessment team in the baseline and follow-up assessments.All data from the baseline and follow-up assessments and reports from sessions (e.g., dates, length of session, manual topic covered) will be captured using mobile technology. The database will be reviewed on a continuous basis by unblinded members of the team to check on quality.The trial statisticians will be asked to review the data at key points during the life of the trial.

Reports will be submitted to the NIMH DSMB twice per year for external control of quality. All serious adverse events will be reported to the NIMH DSMB within 48 hours of being reported to the trial team.

It is expected that participants will experience a number of direct benefits as a result of receiving care in the intervention arm of the trial. These may include improved mood, reduction of symptoms, improved social functioning, stronger social support networks, improved bonding with infant, improved health care utilization by mother and infant, and the development of problem solving skills. In addition to the above direct benefits, the study is likely to yield generalizable knowledge about the outcomes of task sharing counseling interventions for maternal depression. This may inform the development and scaling up of such interventions in routine practice in South Africa and other African countries.

## Discussion

In summary, there is a substantial treatment gap for mental disorders in sub-Saharan Africa, and addressing this treatment gap requires innovative public health strategies, such as task sharing. Maternal depression is a key public health concern, with high prevalence rates reported among deprived communities in the Western Cape and KwaZulu-Natal provinces in South Africa. Maternal depression has negative health consequences for both mothers and their infants. There are a number of potential psychological interventions that have shown benefits in the treatment of maternal depression, but very few have been rigorously evaluated using a task sharing approach in sub-Saharan Africa.

Research to date indicates the need for a RCT to evaluate the effectiveness and cost effectiveness of a task sharing intervention for maternal depression in a low income context, such as Khayelitsha, South Africa. This intervention needs to be contextualized to local needs and tailored for specific disorders. The general principles of task sharing need to be documented in such a way that they identify the common ingredients of effective approaches for mental health services across the sub-Saharan African region. The proposed trial will be the first RCT evaluating task sharing models of delivering care for persons with maternal depression in sub-Saharan Africa.

